# 4. STUDY POPULATION

## 4.1 Population

Twenty obese, type 2 diabetic Caucasian men (BMI>30 kg/m2), age 50-70 yr.

Twenty-two healthy obese Caucasian men (BMI>30 kg/m2), age 50-70 yr

Twenty-two healthy, lean Caucasian men (BMI18-25 kg/m2), age 50-70 yr

Subjects must meet all eligibility criteria for inclusion, including participation in a screening OGTT (not for diabetic subjects), to be able to exclude non-treated diabetics.

## 4.2 Screening visit

Before the screening, volunteers have to give their written informed consent. A general and medical questionnaire will be filled out, containing questions concerning our exclusion criteria. Fasting blood and urine samples will be collected and the following parameters will be determined for all volunteers:

- Fasting plasma glucose
- Fasting urinary glucose
- Fasting plasma insulin
- OGTT (Oral Glucose Tolerance Test)
- Length, weight and waist
- Blood pressure
- Hemoglobin levels

After the screening visit, the participants will receive a breakfast.

### 4.3 Inclusion criteria:

All subjects:

- Male sex
- Age 50-70 years
- Hemoglobin levels>8.4 mmol/L

For diabetic patients only:

- BMI > 30 kg/m2
- Must be on sulphonylurea- or metformin therapy for at least 6 months with a constant dose for at least two months, or on dietary treatment for at least 6 months
- Well-controlled diabetes: fasting plasma glucose concentration must be <10.0 mmol/l at the time of screening.

For obese controls only:

- BMI > 30 kg/m2
- normoglycemic according to WHO criteria (OGTT, fasting blood glucose< 7 mmol/L, after 2 hr <7.8mmol/L)
- Urine glucose concentrations <0,25 g/l
- systolic blood pressure <160 mmHg or diastolic blood pressure < 100 mmHg

For lean controls only:

- - BMI < 25 kg/m2
- normoglycemic according to WHO criteria (OGTT, fasting blood glucose< 7 mmol/L, after 2 hr <7.8 mmol/L)
- Urine glucose concentrations < 0,25 g/l
- systolic blood pressure <160 mmHg or diastolic blood pressure < 100 mmHg

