## 4.4 Exclusion criteria

All subjects:

- Female gender
- Age below 50 or above 70 years
- Allergic to cow milk or dairy products
- Allergic to fish oil
- Vegetarian
- Tobacco smoker
- Current or recent (<4 weeks) use of fish oil supplements or more then four times fish/week; 24.35 g of EPA-DHA of fish per month (800 mg/day) as judged by the questionnaire.
- Received inoculations within 2 months of starting the study or planned to during the study
- Donated or intended to donate blood from 2 months before the study till two months after the study
- Unstable body weight (weight gain or loss > 3 kg in the past three months)
- Medical condition that can interfere with the study outcome (i.e. cardiovascular disease, gastrointestinal disease, renal dysfunction)
- Use of medications know to interfere with glucose homeostasis (i.e. corticosteroids)
- abuse of drugs and/or alcohol
- participation in another biomedical study within 1 month before the first screening visit

For obese, type 2 diabetic subjects only:

- severe diabetes which requires application of insulin
- diabetes-related complications

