### 6.1.2 Measurements of secondary study outcomes

PBMC immune response capacity

Cytokine profiles will be measured in plasma at all time points (T=0, 2 and 4 hrs) by quantitative immunoassays at Rules Based Medicine laboratories (Austin, Texas, USA). The cytokine profile of a panel of 120 proteins including adiponectin, CRP, and interleukins will be determined. For details on these 120 proteins, see: <http://www.rulesbasedmedicine.com/products-services/humanMAP-antigen.asp>

Plasma levels of additional potential biomarkers for metabolic syndrome (i.e. MBL2, FAM3D) will be measured in plasma by ELISA.

PBMC immune response will be determined by stimulation of the isolated cells ex vivo with lipopolysaccharide (LPS) for 4 hours. TNFα secreted in culture medium of the PBMC will be measured by ELISA. PBMC expression of genes involved in the acute immune response will be measured by qPCR.

Leukocyte activation markers will be determined at all time points (T=0, T=2, T=4 hrs) by using flow cytometry analysis (coulter Epics XL.MCL flow cytometry by Beckman Coulter).

Endothelial dysfunction

Macro vascular regional arterial stiffness will be assessed by Pulse Wave Analysis (PWA) (13). This is a non-invasive measurement which will be performed at every time point (T=0, 2 and 4 hrs).

A pressure sensor (applanation tonometer) is applied on the radial artery to record pressure pulse waveforms. The waveform is calibrated using systolic and diastolic pressure values from a conventional cuff measurement. From these peripheral waveforms we can derive a aortic pressure waveform and conduct a pulse wave analysis (PWA). A number of features can be extracted from a PWA, which cannot be made from the conventional measurement of brachial blood pressure. These features include the Augmentation Index (Aix) and the Subendocardial Viability Ratio (SEVR).

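### The blood pressure criterion for the two control groups joins its limits with 'or', so a man with one value raised to any height still qualifies as a healthy control

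*Protocol*

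**What the plan says.** Section 4.3 of the protocol gives separate inclusion lists for all subjects, diabetic patients, obese controls and lean controls. The two control lists carry the same blood pressure item, worded identically: "systolic blood pressure <160 mmHg or diastolic blood pressure < 100 mmHg". The all-subjects list covers sex, age and haemoglobin and has no pressure item. The diabetic list covers BMI, therapy and glucose and has none either.

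Section 4.1 describes both control groups as healthy, for instance "Twenty-two healthy obese Caucasian men (BMI>30 kg/m2), age 50-70 yr", and adds that "Subjects must meet all eligibility criteria for inclusion". Section 4.4 gives no pressure value for any group. The nearest item there, which applies to everyone, is "Medical condition that can interfere with the study outcome (i.e. cardiovascular disease, gastrointestinal disease, renal dysfunction", with the bracket closed after the last condition. Section 4.2 has blood pressure measured at screening in every volunteer.

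Endothelial function is a secondary outcome, assessed by pulse wave analysis. On the method, section 6.1.2 says: "The waveform is calibrated using systolic and diastolic pressure values from a conventional cuff measurement". The third hypothesis in section 2.1 expects more dysfunction after the fat load in the high-risk men than in the healthy men. The Statistical Analysis section compares risk groups by one-way ANOVA and names no covariate.

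**The concern.** A criterion with a systolic and a diastolic limit is normally there to keep out men who exceed either one. In an exclusion list, 'or' does that. In an inclusion list it does the opposite: meeting one limit is enough and the other stops working. As printed, a man with a clearly raised systolic or diastolic pressure enters as a healthy control provided his other value is under its limit.

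What is at stake is the meaning of the healthy reference groups in the between-group vascular comparison. The obese controls are matched to the diabetic men on age and BMI, and the lean controls on age only (section 3.1), so nothing else in the design restrains pressure. With 22 men planned per group, each control admitted this way is 1/22 = 4.5% of his group.

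**Working it through.** The protocol states no figure to reproduce here. The check is of a logical condition.

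**Inputs (section 4.3).** Systolic limit 160 mmHg, diastolic limit 100 mmHg, same wording in both control lists. Write S for systolic and D for diastolic pressure.

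**Rule as printed.** Eligible if S < 160 or D < 100. The negation is S ≥ 160 and D ≥ 100, so only a man at or above both limits is refused.

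**Rule if both limits must hold.** Eligible if S < 160 and D < 100. The negation is S ≥ 160 or D ≥ 100, so a man at or above either limit is refused.

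**Where the two rules differ.** They disagree for men who breach exactly one limit:

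| Reading (mmHg) | S < 160 | D < 100 | As printed ('or') | Both limits ('and') |
| --- | --- | --- | --- | --- |
| 150/90 | yes | yes | eligible | eligible |
| 159/99 | yes | yes | eligible | eligible |
| 190/95 | no | yes | eligible | not eligible |
| 220/99 | no | yes | eligible | not eligible |
| 150/115 | yes | no | eligible | not eligible |
| 159/130 | yes | no | eligible | not eligible |
| 160/100 | no | no | not eligible | not eligible |
| 165/105 | no | no | not eligible | not eligible |

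When D is below 100 the printed rule puts no ceiling on S, and when S is below 160 it puts none on D. It also ranks men oddly: 160/100 is refused while 220/99 is accepted.

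**Does another passage correct it?**
- Section 4.1 requires every criterion to be met. That joins the items in the list to one another; it does not change the 'or' inside one item.
- Section 4.4 excludes interfering conditions for all subjects. It names cardiovascular, gastrointestinal and renal disease, but not hypertension, and sets no value. It leaves room for judgement without restoring either limit.
- The other inclusion items for controls (BMI, glucose tolerance, urine glucose) do not concern pressure.

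**Which analyses are exposed?**
- SFA against MUFA against PUFA within a risk group: each man takes all three shakes and serves as his own reference. Who was admitted affects whom the result describes, not the fairness of the contrast.
- Risk group against risk group for a given shake: the men differ between groups, so the make-up of the control groups enters directly. The pulse wave indices are where blood pressure bears most plainly on the outcome.

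**The case against.** **A likely slip that staff would read through.** The wording was probably carried over from an exclusion-style phrase, and a sensible screener may apply both limits anyway. That is fair, and it is why this is a small correction. But the item appears twice in the same form, nothing elsewhere overrides it, and eligibility should not depend on guessing the intent.

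**The general exclusion is a backstop.** An investigator could refuse a man at 190/95 because his condition might interfere with the vascular outcome. This stands in part: the printed rule makes such a man eligible on the pressure item but does not guarantee his entry. The backstop is discretionary and carries no number.

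**Stronger readings that the protocol does not support.**
- *That all severely hypertensive men can enter as controls.* They cannot: a man at or above both limits is refused.
- *That the missing limit for diabetic men is an error.* The groups are chosen to differ in risk, and a ceiling for men called healthy but not for patients is a coherent choice. It contradicts no other statement, and matching on pressure is never promised. The diabetic men also have their own restrictions, such as "Well-controlled diabetes: fasting plasma glucose concentration must be <10.0 mmol/l at the time of screening" and the exclusion of "diabetes-related complications".
- *That calibrating to cuff pressure makes the indices biased.* Each waveform is calibrated to that man's own measured pressure. This shows that pressure enters the measurement, not that the result is biased.
- *That the group comparisons must be adjusted for blood pressure.* If higher pressure belongs to the risk phenotype, adjustment could remove part of the difference under study. It is a debatable trade-off.
- *That the primary outcome is compromised.* Nothing in the protocol shows an effect on PBMC gene expression.

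**Conclusion.** The criterion is wrong as written. It excludes only men with systolic pressure of at least 160 and diastolic pressure of at least 100 mmHg together, and admits as healthy controls men with one value raised without bound. This follows from the text alone and rests on no outside figure.

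The consequence is narrow. It concerns between-group comparisons, chiefly augmentation index and subendocardial viability ratio, both secondary. The within-man comparison of shakes is protected by the crossover. Neither the share of men aged 50-70 with exactly one value over its limit nor the effect of such men on the group means is given, so neither the size nor the realised direction of any distortion can be stated. The correction assumes that both printed limits were meant to bind, which is the only reading under which each does any work on its own.

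**What to change.** In section 4.3, replace 'or' with 'and' in the blood pressure item of both the obese and the lean control list, so that a control must be under both limits already printed. No new threshold, measurement or analysis is needed, since pressure is already taken at screening. The cost is one word in two lines and a few more screening failures among controls.

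Optionally, add a sentence saying whether the absence of a pressure limit for the diabetic group is intended. That is a clarification only; a blood-pressure-adjusted analysis is not required.

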## 4.4 Exclusion criteria

All subjects:

- Female gender
- Age below 50 or above 70 years
- Allergic to cow milk or dairy products
- Allergic to fish oil
- Vegetarian
- Tobacco smoker
- Current or recent (<4 weeks) use of fish oil supplements or more then four times fish/week; 24.35 g of EPA-DHA of fish per month (800 mg/day) as judged by the questionnaire.
- Received inoculations within 2 months of starting the study or planned to during the study
- Donated or intended to donate blood from 2 months before the study till two months after the study
- Unstable body weight (weight gain or loss > 3 kg in the past three months)
- Medical condition that can interfere with the study outcome (i.e. cardiovascular disease, gastrointestinal disease, renal dysfunction)
- Use of medications know to interfere with glucose homeostasis (i.e. corticosteroids)
- abuse of drugs and/or alcohol
- participation in another biomedical study within 1 month before the first screening visit

For obese, type 2 diabetic subjects only:

- severe diabetes which requires application of insulin
- diabetes-related complications

# 5. INTERVENTION

##

## 5.1 Intervention meals

The high-fat shakes the participants will consume on each study day will contain 95 g fat each, and the total volume of each milkshake to be consumed will be 500 ml. The fatty acid composition is the only component that will differ between the milkshakes.

The basal constituent of all three milkshakes will be whipped cream and for every milkshake extra amounts of the specific fats of interest (i.e SFA, MUFA or PUFA) will be added. Water will be added to reach a total volume of 500 ml. For the composition of the milkshakes see table 2.

Table 2 : composition of the shakes

|  | | | **SFA shake** | **MUFA shake** | **PUFA shake** |
| --- | --- | --- | --- | --- | --- |
| Basal constituent (whipped cream) | | |  | | |
| Protein (g) | | | 3 | 3 | 3 |
| Carbohydrates (g) | | | 22 | 22 | 22 |
| Fat (g) | | | 40 | 40 | 40 |
| Extra added fat | | |  | | |
| Fat (g) | | | 55 | 55 | 55 |
|  | SFA (g) | | 45 | 10 | 10 |
| MUFA (g) | | 10 | 45 | 10 |
| PUFA (g) | | - | - | 35 |
|  | Of which EPA/DHA (g) | - | - | 22 |
| **Total** | | |  | | |
| Fat (g) | | | 95 | 95 | 95 |
| Energy (KJ) | | | 3938 | 3938 | 3938 |

## 5.2 Guidelines during the study period

All participants will be advised to keep the same dietary habits as before the study period. In order to standardize the participants‘ nutritional status before each testing day, the participants will be asked to:

- Consume a low fat evening meal (<10 g) the day before each study day (will be provided) and not to eat fish on the day before the study day
- Refrain from alcohol the day before each study day
- Avoid strenuous exercise the day before each study day
- Fast overnight before each study day (min of 10 hours).
- Transport to the university should be similar every study day

Details on how to live up to these guidelines will be given (and discussed) to each participant before the start of the study.

# 6. METHODS

## 6.1 Study outcomes

### 6.1.1 Measurements of primary study outcomes

PBMC gene expression

Gene expression changes will be assessed using whole genome Affymetrix microarrays for the samples at all time points.

### 6.1.2 Measurements of secondary study outcomes

PBMC immune response capacity

Cytokine profiles will be measured in plasma at all time points (T=0, 2 and 4 hrs) by quantitative immunoassays at Rules Based Medicine laboratories (Austin, Texas, USA). The cytokine profile of a panel of 120 proteins including adiponectin, CRP, and interleukins will be determined. For details on these 120 proteins, see: <http://www.rulesbasedmedicine.com/products-services/humanMAP-antigen.asp>

Plasma levels of additional potential biomarkers for metabolic syndrome (i.e. MBL2, FAM3D) will be measured in plasma by ELISA.

PBMC immune response will be determined by stimulation of the isolated cells ex vivo with lipopolysaccharide (LPS) for 4 hours. TNFα secreted in culture medium of the PBMC will be measured by ELISA. PBMC expression of genes involved in the acute immune response will be measured by qPCR.

Leukocyte activation markers will be determined at all time points (T=0, T=2, T=4 hrs) by using flow cytometry analysis (coulter Epics XL.MCL flow cytometry by Beckman Coulter).

Endothelial dysfunction

Macro vascular regional arterial stiffness will be assessed by Pulse Wave Analysis (PWA) (13). This is a non-invasive measurement which will be performed at every time point (T=0, 2 and 4 hrs).

A pressure sensor (applanation tonometer) is applied on the radial artery to record pressure pulse waveforms. The waveform is calibrated using systolic and diastolic pressure values from a conventional cuff measurement. From these peripheral waveforms we can derive a aortic pressure waveform and conduct a pulse wave analysis (PWA). A number of features can be extracted from a PWA, which cannot be made from the conventional measurement of brachial blood pressure. These features include the Augmentation Index (Aix) and the Subendocardial Viability Ratio (SEVR).

### 6.1.3 Measurements of tertiary study outcomes

Plasma lipids, glucose and insulin

Plasma lipid profile, glucose and insulin will be determined at all time points (T=0, T=2, T=4 hrs).

Monocyte and lymphocyte gene expression

T-cells and monocytes will be isolated via a negative selection procedure from PBMC using magnetic cell separation (MACS) tubes (Miltenyi Biotec). Gene expression changes in these cells will be assessed using whole genome Affymetrix microarrays for the samples at all time points.

Phenotype measurements

Body composition will be measured with the use of the BodPod.

MRI will be used to measure abdominal fat distribution, i.e. intra-abdominal fat and subcutaneous abdominal fat. In short, axial T1-weighted spin echo images will be acquired with a Philips Gyroscan NT Intera 1.0T scanner using the body coil with the patient in supine position. Slices will be centred at the interspace L4-L5, with the other slices situated above and below to cover the whole abdomen. A breath–hold technique will be applied to avoid breathing induced artefacts.

Measurements will be performed in collaboration with the Department of Radiology, Hospital Gelderse Vallei. All the measurements will be performed as much as possible by the same technician, and at the same time of the day. A experienced radiologist will evaluated all scans made

Fecal micro flora profiling will be done of feces collected at one time point in the study period.

## 6.2 Randomisation and blinding

Before the start of the study, participants of each ‘risk profile group’ will be randomly allocated to one of the six intervention groups (see table 1). The shakes will be labeled with three different codes. Participants will not know which code is allocated to which shake.

## 6.3 Study procedures

### 6.3.1 Information meeting

An information meeting will be organized 6 weeks before start of the study. In this meeting the investigators will explain the background, objectives and set up of the study. Also the possible risks and burdens will be explained and during this meeting there will be time for the potential participants to ask questions.

### 6.3.2 Screening

There will be a screening visit planned 4 weeks prior of the beginning of the study in order to recruit participants who fulfill all criteria. The following data will be collected:

- Written informed consent
- 3 ml of blood for fasting blood glucose
- Fasting urinary glucose concentrations
- Oral glucose tolerance test
- Length, weight and waist
- Blood pressure values
- A general and medical questionnaire will be filled out

### 6.3.3 Preparations prior to the Intervention

All participants will receive a diary 2 weeks prior to the study. In this diary, the participants can keep track of any signs of illness, any deviations from the protocol or any experienced side effects. In addition, further details (e.g. logistical) of the experiment will be elucidated.

### 6.3.4 Intervention

Figure 1 shows the study design and table 3 summarizes the assessments performed during the intervention.

Before the start of each study day, the Hb value of each participant will be determined by using a hemoglobin analyzer (HemoCue 201). Participants with a Hb value below 8.4 mmol/L will not be measured and are asked to make a new appointment. If Hb values are normal (e.g. above 8.4mmol/L) the measurements can be started. At T=-20 min, macro vascular regional arterial stiffness will be assessed and blood samples (62 ml) will be drawn by normal venopuncture. At T=0, the high-fat milkshake will be consumed within 15 min. Blood will be drawn 2 hours and 4 hours after intake of the shake and macro vascular regional stiffness will be assessed at the same time points.

The participants will spend the entire study duration (4.5 hours) in a room close to the blood collection room, where they will be able to read books, watch television, video or DVDs, or relax in comfortable chairs. At the end of the study day a lunch will be offered to the participants. At the end of the three study days the diaries will be collected*.*

SFA

SFA

SFA

MUFA

MUFA

MUFA

PUFA

PUFA

PUFA

SFA

SFA

SFA

MUFA

MUFA

MUFA

PUFA

PUFA

PUFA

SFA

SFA

SFA

MUFA

MUFA

MUFA

PUFA

PUFA

PUFA

Obese, diabetic subjects

Obese, healthy subjects

Lean, healthy subjects

Study day 1

Study day 2

Study day 3

Washout >1 wk

Washout >1 wk

Study day 1

Study day 2

Study day 3

T=0,2,4 hrs:

- Blood sampling

- Endothelial function measurement

T=0,2,4 hrs:

- Blood sampling

- Endothelial function measurement

T=0,2,4 hrs:

- Blood sampling

- Endothelial function measurement

Figure 1: Design of the study

Table 3: Protocol on each study day.

| **Intervention time, after 10h overnight fast** | **-20 min**  (7.00am) | **0 hr**  (7.20am) | **2 hr**  (9.20 am) | **4 hr**  (11.20 am) |
| --- | --- | --- | --- | --- |
| Consumption of high fat shake |  | x |  |  |
| Blood sampling (ml) | x |  | x | x |
| for plasma/serum isolation | 20 ml |  | 20 ml | 20 ml |
| for PBMC isolation | 42 ml |  | 42 ml | 32 ml |
| PBMC gene expression | x |  | x | x |
| PBMC stimulation with LPS | x |  | x |  |
| Cytokine profile | x |  | x | x |
| Plasma fatty acid profile | x |  | x | x |
| Plasma insulin and glucose | x |  | x | x |
| Endothelial function | x |  | x | x |
| Leukocyte activation markers | x |  | x | x |

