# 3. STUDY DESIGN

## 3.1 Intervention study

This study is a single-blind cross-over intervention (challenge) study, planned to run from the end of October till half December 2009.

In this study obese type 2 diabetic subjects will be studied and compared to age and BMI matched healthy obese controls and to age-matched healthy lean controls.

A total of 22 type 2 diabetic obese men, 22 obese men and 22 lean men will consume high-fat milkshakes containing 95 g of fat, mainly consisting of either SFA, MUFA or PUFA. No differences can be seen or tasted between the shakes.

The 22 type 2 diabetic obese, 22 obese and 22 lean men will be randomly divided in 6 groups to determine in which order they will receive the milkshakes. The groups will receive a different high-fat shake every two weeks (see table 1). There will be a minimal period of one week between two testing days, in order to exclude carry over effects. Six persons will be evaluated on each testing day.

Table1: Experimental study design

|  |  | Week 1/2 | Week 3/4 | Week 5/6 |
| --- | --- | --- | --- | --- |
| Intervention order | Group 1 | SFA | MUFA | PUFA |
| Group 2 | SFA | PUFA | MUFA |
| Group 3 | MUFA | SFA | PUFA |
| Group 4 | MUFA | PUFA | SFA |
| Group 5 | PUFA | SFA | MUFA |
| Group 6 | PUFA | MUFA | SFA |

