## 7.2 Adverse and serious adverse events

Adverse events (AE) are defined as any undesirable experience occurring to a participant during a clinical trial, whether or not considered related to the investigation. All AE reported by the participant or observed by the investigators will be recorded.

A serious adverse event (SAE) is any untoward medical occurrence or effect that at any dose results in death:

- Is life threatening (at the time of the event)
- Requires hospitalization or prolongation of hospitalization.
- Results in persistent or significant disabilities or incapacity
- Is a congenital anomaly
- Is a new event of the trial likely to affect the safety of the participants, such as an unexpected outcome of an adverse reaction, lack of efficacy of an IMP used for the treatment of a life threatening disease, major safety finding from a newly completed animal study, etc.

All SAE will be reported to the accredited METC that approved the protocol, according to the requirements of that METC.

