## 10.3 End of study report

The investigator will notify the accredited METC of the end of the study within a period of 8 weeks. The end of the study is defined as the last day of the intervention. In case the study is ended prematurely, the investigator will notify the accredited METC, including the reasons for the premature termination.

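### Read naturally, section 6.3.4 takes the side-effect diary back when study day 3 closes, leaving the third shake roughly 4 hours of diary cover against at least one week after the first two

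*Protocol*

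**What the plan says.** All of these are in the Protocol.

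- **Purpose of the diary (6.3.3).** It is handed out two weeks before the study. "In this diary, the participants can keep track of any signs of illness, any deviations from the protocol or any experienced side effects".
- **Return of the diary (6.3.4).** "At the end of the three study days the diaries will be collected". The sentence just before it places the lunch at the close of the study day, in parallel wording.
- **Length of the visit (6.3.4 and Table 3).** "The participants will spend the entire study duration (4.5 hours) in a room close to the blood collection room". Table 3 puts the baseline measurements at 7.00, the shake at 7.20 and the last blood sample at 11.20.
- **Spacing of visits (3.1).** "There will be a minimal period of one week between two testing days, in order to exclude carry over effects".
- **Adverse-event rule (7.2).** "All AE reported by the participant or observed by the investigators will be recorded". No end date and no scheduled contact is attached to this rule.
- **Expected effects (9.4.3).** Mild gastrointestinal discomfort in rare cases (belching, flatulence, loose stools), a fatty or fishy aftertaste, and local haematoma, bruising or pain from venepuncture. No onset times are given.
- **Contacts (9.4.3, Table 4).** An information meeting, screening, three study days and an MRI visit. The MRI has no fixed date, and no follow-up visit or call is listed.

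**The concern.** The diary is the only structured means the protocol describes for recording side effects at home. Several of the effects that the protocol itself names could be noticed only after the man has left the university. After the first and second study days he still has the diary, and he also comes back for another study day, when staff can hear of a problem or see it. After the third study day he has neither, on the natural reading of 6.3.4.

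What is at stake is the completeness of adverse-event recording after one third of the shakes and after the blood draws of the third visit. Unlike a detail left for later, this is a collection rule stated in the protocol. Following it as written produces the unequal cover.

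**Working it through.** The protocol gives no figure for diary cover, so there is none to reproduce. The check is clock and calendar arithmetic.

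**1. Cover after the third shake.** Inputs: visit start 7.00 and shake 7.20 (Table 3); visit length 4.5 h (6.3.4).
- End of visit: 7.00 + 4.5 h = 11.30.
- From the start of the shake: 11.30 − 7.20 = 4 h 10 min.
- From the latest end of drinking (15 minutes allowed, so 7.35): 11.30 − 7.35 = 3 h 55 min.

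The times are rounded and a lunch is offered at the end of the day, so the supportable statement is roughly 4 hours.

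**2. Cover after the first and second shakes.** Input: at least one week between testing days (3.1).
- 7 × 24 h = 168 h as a minimum.
- Against 4 h 10 min (4.17 h), the ratio is 168 / 4.17, or about 40 to 1.

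**3. Number of exposures with the short cover.** Input: three groups of 22 men (3.1 and 4.5).
- Men: 3 × 22 = 66. Planned exposures: 66 × 3 = 198.
- Third exposures: 66, and 66 / 198 = 33%.
- Section 4.1 gives twenty diabetic men instead of 22. That would make 64 of 192 exposures, still one third.

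**4. Spread over the shake types.** Input: Table 1. PUFA is third in groups 1 and 3, MUFA in groups 2 and 5, SFA in groups 4 and 6. Each shake is therefore third in 2 of 6 sequences.
- Expected number per shake: 66 × 2/6 = 22.
- 22 men do not divide evenly by 6. If each risk group fills the sequences as evenly as possible (4+4+4+4+3+3), a given shake is third for 6 to 8 men per risk group, so for 18 to 24 over the three groups.

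The short cover thus falls about equally on the three shakes.

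**5. Number of missed events.** This cannot be estimated, because the protocol gives neither event rates nor onset times.

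**The case against.** **The collection sentence gives no clock time.** It could mean some time after the three days are over. That is possible and cannot be excluded. But the parallel wording about the lunch points to the close of the third visit, and no later visit, call or postal return is described. If later collection is meant, the text should say so.

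**Holding a diary is not the same as recording adverse events.** This stands. Use of the diary is optional, 7.2 does not mention it, and 7.3 follows every adverse event until it has abated or is stable. A reader might infer that adverse-event recording stops about 4 hours after the third shake. The documents do not support that: a participant can still report. What is lost is the prompt, and 7.3 helps only once an event is known.

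**The week is a washout, not a safety window.** Also true: 3.1 sets it to exclude carry-over, and nothing says that a week of observation is needed after one shake. The point is only that the first two shakes get this cover anyway and the third does not.

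**Stronger readings that do not hold.**
- A reader might combine the definition of an adverse event as "any undesirable experience occurring to a participant during a clinical trial" (7.2) with 10.3, where "The end of the study is defined as the last day of the intervention", and conclude that effects starting the next day fall formally outside the study. Section 10.3 serves to set the notification to the ethics committee. Nothing in 7.2 refers to it, and the follow-up rule in 7.3 and the insurance cover in 9.5 both allow for safety matters after that date.
- A reader might also subtract the last draw time from the end of the visit and count the diary cover of that draw in minutes. The times are too rounded for that. If the 4 hours run from the end of drinking, the draw would fall at about 11.35, after the computed end of the visit.

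**Conclusion.** The point holds as a minor one. On the natural reading of 6.3.4, 66 of 198 planned exposures (33%; about 22 per shake, 18 to 24 under even allocation) have roughly 4 hours of diary cover, against at least 168 hours for the other 132. Effects that begin at home after study day 3 then depend on unprompted reports under 7.2.

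The consequence is less complete adverse-event recording after the last shake, and it stops there. The study-day measurements behind the primary, secondary and tertiary outcomes end at the 4-hour time point and do not draw on the diary. No tolerability comparison is planned, and a reader who inferred material bias between shakes would be overlooking the rotation in Table 1.

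The conclusion rests on three assumptions: that the diary is collected when the third visit closes, that the visit runs about 4.5 hours from 7.00, and that no contact after day 3 is arranged outside the protocol. How many events would be missed is unknown; the protocol expects the gastrointestinal effects to be mild and rare.

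**What to change.** In 6.3.4, replace the collection sentence with:

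> Participants keep the diary until one week after study day 3 and return it by post or at any remaining visit; pages filled in so far are copied on study day 3.

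In 7.2, add:

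> Adverse events are recorded until one week after each participant's study day 3.

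All three shakes then have the same minimum diary cover of one week.

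The cost is two sentences, a reply envelope for each of 66 men, and copying on day 3. No visit or procedure is added. The downside is that some diaries will be returned late or lost; because of the copy, a lost diary costs only the last week.

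The sponsor should check the calendar. The summary gives a study period of 8 weeks and Table 1 ends in week 5/6, but the protocol does not say when the 8 weeks start. If they include the two weeks of diary use before the study, 2 + 6 = 8 and the period is already full. Appointments remade because of a low haemoglobin value could also move day 3 later. The stated study period may therefore need a small extension.
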